### Internal feasibility study

A two-stage internal feasibility study will be conducted to examine methods of patient invitation and rates of recruitment, before proceeding with the main trial. The first feasibility phase will last for a minimum of 3 months and aim to recruit approximately 25 participants from a minimum of 3–5 practices. The aim will be to establish whether or not anyone will be willing to participate in the study.

The second feasibility phase will focus on recruitment rates for the main trial and whether the intended sample size is likely to be met during the recruitment period. This phase will have a recruitment target of 75 participants from 10 practices over 6 months, giving a total sample for the feasibility study of 100 participants. A recruitment rate of 15% of invitations sent is expected. The following actions will be considered to address varying rates of recruitment at the end of the feasibility phases:If ≥100 participants are recruited, trial will proceed as planned.If 75–99 participants are recruited, recruitment materials/method will be re-examined and edited where necessary following discussions with stakeholders and patient and public involvement representatives.If 50–74 participants are recruited, the allocation of resources and recruitment criteria will be re-examined using information gathered from concurrent qualitative work.If <50 participants are recruited, the Trial Steering Committee (TSC) will decide, in discussion with the Data Monitoring and Ethics Committee (DMEC) and the funders, whether the trial should be stopped due to futility.

### Sample size calculation

Assuming that 100% of participants in the usual care group, and 96% of those in the medication reduction group have controlled systolic blood pressure levels (<150 mm Hg) at follow-up, approximately 540 participants will be required to detect a non-inferior difference in systolic blood pressure control between groups. Calculations assume a 10% non-inferiority margin, 90% power, 2.5% one-sided level of significance, 10% loss to follow-up and a 10% dilution effect due to cross-over between arms. There is no existing precedent for an appropriate margin of non-inferiority in this type of trial, but 10% was deemed useful to inform future doctor-patient discussions about medication reduction: if the non-inferiority margin is met, it will suggest that for every 10 patients who have their medication reduced, at least 9 will still have controlled blood pressure at 12-week follow-up.

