### Statistical analysis

A detailed statistical analysis plan will be agreed prior to the end of the trial. The primary and secondary analyses will be by intention to treat (ITT), unless stated otherwise. The primary analysis will be a non-inferiority analysis by means of the ‘two one-sided test’ procedure,^32^ whereby the 95% CI for the relative risk of participants with systolic blood pressure at 12 weeks below 150 mm Hg between the medication reduction group and the usual care group is calculated. This will be obtained by means of a generalised linear mixed effects model with GP surgery included as a random effect and baseline blood pressure as a fixed effect. If the lower limit of the CI is >0.9 (equal to a risk difference of 10%) then the research hypothesis that medication reduction will be non-inferior in terms of blood pressure control to usual care will be accepted. As a secondary analysis of the primary outcome, a per-protocol (PP) analysis will be performed, since ITT can be anticonservative for a non-inferiority hypothesis.^32^ Participants who received the medication reduction intervention in the PP analysis will be defined as a participant in the medication reduction arm who maintained their medication reduction throughout the 12-week follow-up period.

Secondary analyses will examine the proportion of participants in the medication reduction arm who maintained their medication reduction throughout the 12-week follow-up period. Secondary outcomes will be analysed by means of linear mixed effects models, adjusting for the baseline level of the outcome and baseline systolic blood pressure and including practice as a random effect: systolic blood pressure, EQ-5D-5L and the Frailty index/frail scale. The difference in the rate of side effects and AEs between the medication reduction and usual care arms will be analysed by means of a logistic mixed effects model adjusting for baseline systolic blood pressure and including practice as a random effect.

Exploratory subgroup analyses of blood pressure control, change in blood pressure and maintenance of medication reduction will be conducted by different levels of baseline frailty, functional independence, cognitive function, number of medications prescribed at baseline and number of comorbidities at baseline.

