## Discussion

Current guidelines in the UK suggest that doctors should ensure that patients are fully informed of the benefits and risks of their prescribed medications and where appropriate, discuss the potential for medication withdrawal in frail individuals with multimorbidity.^35^ This is difficult given consultation time constraints and fear that deprescribing might result in harm.^36^ This is compounded by conflicting and inconclusive evidence about the benefits and harms of treatment, and a lack of evidence about what will happen if these treatments are reduced.

The ECSTATIC trial enrolled 1067 younger participants aged 40–70 years, taking antihypertensives for primary prevention of cardiovascular disease.^18^ The trial demonstrated that only 27% of participants were able to maintain medication reduction throughout follow-up and at 3 months, systolic blood pressure was on average 6 mm Hg higher in the deprescribing group. At 2-year follow-up, the risk of uncontrolled blood pressure was significantly higher in those patients attempting to deprescribe. Unlike the present study, the medication reduction algorithm used did not encourage reintroduction of therapy if blood pressure was persistently raised.

The Discontinuation of Antihypertensive Treatment in Elderly people (DANTE) study^16^ examined the effect of complete antihypertensive medication discontinuation in 385 patients over the age of 75 years and with mild cognitive deficits. After 16 weeks of follow-up, they observed a 7/3 mm Hg increase in blood pressure but no difference in overall cognition compound score or quality of life between groups. A study by van der Wardt *et al*
19 examined the feasibility of a trial reducing antihypertensives in patients with dementia, but was only able to recruit nine participants for the withdrawal programme (1% recruitment rate) and a larger trial was deemed unfeasible. Similarly, the Opti-Med trial^37^ demonstrated in 95 participants that a broader deprescribing approach is achievable in patients living in nursing homes, but was unable to examine the effect on clinical outcomes due to recruitment issues resulting in only 38% of the planned sample size being enrolled.

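### The 10% cross-over dilution enlarges the sample size, but under the primary ITT non-inferiority test cross-over raises power and threatens type I error, so 540 does not correspond to 90% power

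*Protocol article*

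**What the plan says.** The protocol article, Sample size calculation, sets the expected rates of controlled systolic pressure: "Assuming that 100% of participants in the usual care group" and "96% of those in the medication reduction group have controlled systolic blood pressure levels". It continues: "Calculations assume a 10% non-inferiority margin", "90% power, 2.5% one-sided level of significance", and then "10% loss to follow-up and a 10% dilution effect due to cross-over between arms". The result is about 540 participants. The section names neither the test behind the calculation nor the way in which the dilution was applied.

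The Statistical analysis section states: "The primary and secondary analyses will be by intention to treat (ITT), unless stated otherwise". Non-inferiority is declared if the lower 95% confidence limit for the relative risk exceeds 0.9. The same section warns that ITT can be anticonservative for a non-inferiority hypothesis and adds a per-protocol analysis as a secondary analysis for that reason.

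**The concern.** In a superiority trial, cross-over shrinks the effect to be detected, and enlarging the trial by 1/(1 − c)² restores the power. In a non-inferiority trial analysed by ITT, power depends on the distance between the expected difference and the margin. If participants in one arm take on the other arm's treatment and outcome, the expected difference shrinks and that distance grows. Fewer participants are then needed for the same power.

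Two things are at stake. The stated size and the stated power should correspond, and they do not. The Sample size calculation also presents cross-over as a loss of power that numbers can make good, whereas under this analysis it is a possible source of false non-inferiority that numbers cannot make good.

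**Working it through.** **Inputs** (Sample size calculation): control 1.00, intervention 0.96, margin 0.10, one-sided alpha 0.025 (z = 1.96), power 0.90 (z = 1.2816), loss 0.10, dilution 0.10. Allocation is 1:1 (Randomisation section). The work is on the risk-difference scale. With control at 100%, a relative risk of 0.9 and a difference of 10 points are the same limit.

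**Reproducing 540.** In the Farrington-Manning score test, the null variance uses the restricted rates 1.00 and 0.90, so it is 0.90 × 0.10 = 0.09. The variance under the alternative is 0.96 × 0.04 = 0.0384.

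- n per arm = (1.96·√0.09 + 1.2816·√0.0384)² / 0.06² = 195.6, so 196, or 392 in total
- loss: 392/0.9 = 435.6, so 436
- dilution: 435.6/0.9² = 537.7, that is, about 540

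Dividing by 0.8 instead of 0.81 gives 544, which is also close. A single 1/0.9 for dilution gives 484, which is not. Other standard formulas with the same loss and 1/0.81 factors give 291 (log relative risk), 310 (unpooled), 316 (pooled), 398 (unpooled, continuity-corrected) and 628 (Farrington-Manning, continuity-corrected). Before any dilution step, the largest of these is 458/0.9 = 509. So every route tried that reaches 540 has dilution increasing N.

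Because n varies as 1/distance², the factor 1/0.81 amounts to shrinking the distance to the margin from 6.0 to 5.4 points. That is the opposite of what cross-over does under ITT.

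**Cross-over in the direction it acts.** Assumption: 10% cross over at random and take the other arm's rate.

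| Scenario | Rates | Distance to margin | n per arm for 90% | Total with 10% loss |
|---|---|---|---|---|
| None | 100% v 96% | 6.0 points | 196 | 436 |
| Intervention arm only | 100% v 96.4% | 6.4 points | 167 | 372 |
| Both arms | 99.6% v 96.4% | 6.8 points | 158 | 352 |

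**Power of 540.** Evaluable: 540 × 0.9 = 486, or 243 per arm.

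- No cross-over: Φ[(0.06 − 1.96·√(0.09/243)) / √(0.0384/243)] = Φ(1.77) = 96.2%
- One-way: Φ[(0.064 − 1.96·√(0.09/243)) / √(0.0347/243)] = Φ(2.20) = 98.6%
- Two-way, with restricted rates recomputed: 99.0%

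**Type I error at 243 per arm.** Take a true difference equal to the margin, 100% v 90%.

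- One-way cross-over gives observed rates of 100% v 91%: Φ[(0.01 − 1.96·√(0.09/243)) / √(0.0819/243)] = Φ(−1.51) = 6.6%
- Two-way gives 99% v 91%: about 14%

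A larger N makes this worse. In the one-way case, 196 per arm gives Φ[(0.01 − 1.96·√(0.09/196)) / √(0.0819/196)] = Φ(−1.57) = 5.9%, against 6.6% at 243.

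**The case against.** **The formula is inferred.** This stands. Neither the test nor the dilution factor is printed, and the planned analysis is a mixed model for the relative risk rather than a Farrington-Manning test. The figures of 436 and 96% depend on that method; the unpooled formula would put the power of 540 above 99.7%. The direction does not depend on it. A reader might infer that 540 is an arithmetical slip, but it reproduces from the stated inputs. The fault lies in which way the dilution was made to act.

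**The error is safe for power.** This also stands. The trial is larger than 90% power requires at the stated rates, and nothing here suggests that it is short of participants.

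**The extra size protects the per-protocol analysis.** It helps, but it does not explain 540. Excluding 10% for cross-over needs 392/0.9/0.9 = 484. At 540, about 219 per arm would remain, with power of about 94%. The section also speaks of dilution, not exclusion.

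**The bias is already recognised.** Correct. A reader might infer that the protocol hides the risk of false non-inferiority; the Statistical analysis section names it and adds a per-protocol analysis. What remains is that the two sections treat cross-over differently.

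**Reintroduction belongs to the strategy.** Partly right. The trial compares strategies, and the Intervention group section expects medication to be re-adjusted when pressure stays raised. Narrowing from that source is part of the estimand and may already be in the assumed 96%. Only the remaining cross-over is bias.

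**The 10% looks too low.** The Discussion reports an earlier trial in which "only 27% of participants were able to maintain medication reduction throughout follow-up", and a reader might take this to contradict the 10%. It does not. Those participants were aged 40–70 years, with results reported to 2 years; here they are aged 80 or over and followed for 12 weeks. Failure to maintain reduction is also not the same quantity as cross-over between arms.

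**Conclusion.** The point holds. The dilution adjustment has the wrong direction for the primary ITT non-inferiority test, and 540 does not correspond to 90% power under the stated assumptions. By the Farrington-Manning method, about 436 gives 90% and 540 gives about 96%, rising to 98.6–99.0% with 10% cross-over. The dilution step adds about 102 to 104 participants (538 or 540 less 436).

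The consequence that matters is for type I error: about 6.6% or 14% in place of 2.5% at the margin. These figures rest on cross-over independent of outcome, crossers taking the other arm's rate, and normal approximations. They do not apply to reintroduction that is part of the strategy. The documents do not support a claim that the trial is underpowered or that the bias was overlooked. This is a mismatch to correct in the text, not a flaw in the size of the trial.

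**What to change.** In the Sample size calculation:

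- Remove the dilution inflation and name the method used.
- State that, at 100% v 96% with 10% loss, about 436 gives 90% power and 540 gives about 96%.
- Describe cross-over as a potential anticonservative bias under ITT, consistent with the Statistical analysis section and its per-protocol analysis, and separate it from reintroduction that forms part of the strategy.

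If the extra size is presented as cover for usual-care control below 100%, give its limits. With the 4-point difference kept and 243 evaluable per arm, power is about 90% at 99% v 95%, 84% at 98% v 94% and 78% at 97% v 93%.

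The cost is text only. Enrolment, the decision rule and the planned analyses are unchanged.

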### Randomisation

Consenting participants will be individually randomised (1:1 allocation ratio) to one of two study arms using a fully validated web-based system (Sortition) with manual telephone back up. Participants will not be randomised until after consent has been taken and baseline assessments have been completed. A computer-generated non-deterministic algorithm, minimising on practice and baseline systolic blood pressure will be used to ensure these covariates are balanced between the two intervention arms.

The study will use an open-label design, so patients and practitioners will not be blinded to the intervention or study end points. Therefore, codebreaking will not be necessary. The statistical analysis will be performed blind to patient allocation.

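### Meeting the relative-risk margin bounds control in the reduction arm only relative to usual care, so the 9-in-10 interpretation follows only if usual-care control is 100%

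*Protocol article*

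**What the plan says.** The Sample size calculation section plans on full control under usual care: "Assuming that 100% of participants in the usual care group, and 96% of those in the medication reduction group" are controlled at follow-up. It states that there is no precedent for the margin and that 10% was chosen as useful for discussions between doctors and patients. The reason given is what a successful trial would mean: "it will suggest that for every 10 patients who have their medication reduced, at least 9 will still have controlled blood pressure at 12-week follow-up".

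The Statistical analysis section defines the test on a different quantity: "the 95% CI for the relative risk of participants with systolic blood pressure at 12 weeks below 150 mm Hg", reduction versus usual care. If the lower limit exceeds 0.9, which the article equates with a 10% risk difference, "then the research hypothesis that medication reduction will be non-inferior in terms of blood pressure control to usual care will be accepted". The primary analysis is by intention to treat. The article describes no comparison of the reduction-arm proportion with 90%.

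**The concern.** The 9-in-10 sentence concerns one arm: the proportion controlled among patients whose medication is reduced is at least 90%. The test concerns a ratio of two arms. A ratio above 0.9 sets no fixed floor under the numerator, because the floor moves with control in the usual-care arm. The two statements agree only when usual-care control is exactly 100%, and the sentence is not made conditional on that.

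This matters because the sentence is the only rationale given for the margin and is intended for use with patients. If some usual-care participants are uncontrolled at 12 weeks, the trial can meet its margin while reduction-arm control is below 9 in 10. That is plausible: entry rests on the mean of two readings at a single screening visit, and the outcome on one clinic visit 12 weeks later. Patients and GPs could then be told something the test did not examine.

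**Working it through.** **Inputs.** From the Sample size calculation section: control 100% versus 96%; "10% non-inferiority margin, 90% power, 2.5% one-sided level of significance, 10% loss to follow-up and a 10% dilution effect due to cross-over between arms"; total 540. From the Randomisation section: 1:1 allocation. Analysed per arm after 10% loss: 540 × 0.9 / 2 = 243. Assumed: usual-care control below 100%, since the article gives no other figure.

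**1. The plan's own figure.** A non-inferiority calculation for a risk difference, with the null variance taken at 100% versus 90%, gives

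n per arm = (1.96 × √0.09 + 1.2816 × √0.0384)² / 0.06² = 195.6.

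The total is 2 × 195.6 = 391.2. Dividing by 0.9 for loss and by 0.9² for dilution gives 537; dividing by 0.9 and by 0.8 gives 543. The article does not name its formula, but both results are close to 540. The null point in this calculation, 100% versus 90%, is the one place where the 9-in-10 message and the test coincide.

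**2. What the rule guarantees.** If the relative risk exceeds 0.9, reduction-arm control exceeds 0.9 × usual-care control.

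| Usual-care control | Implied floor for the reduction arm |
|---|---|
| 100% | 90.0% |
| 98% | 88.2% |
| 95% | 85.5% |
| 92% | 82.8% |
| 90% | 81.0% |

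A 10-point risk-difference margin behaves the same way (85% at usual care 95%, 80% at 90%), so the point does not depend on the choice of scale.

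**3. Can the rule be met with observed control below 90%?** Lower limit = exp{ln RR − 1.96 × √[(1 − p₁)/a + (1 − p₀)/c]}, where a and c are the numbers controlled under reduction and usual care.

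- Reduction 214/243 (88.1%), usual care 224/243 (92.2%): RR = 0.9554, SE = √(0.000558 + 0.000349) = 0.0301, lower limit = exp(−0.0457 − 0.0590) = 0.901. The rule is met.
- Reduction 211/243 (86.8%), usual care 219/243 (90.1%): RR = 0.9635, SE = 0.0328, lower limit 0.903. The rule is met.
- Usual care 243/243: the smallest reduction-arm count that passes is 227/243 (93.4%). Under the planning assumption the problem does not arise.

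**4. How often, when the message is false.** True reduction-arm control is set at 89%, with 243 per arm and the unadjusted interval above.

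| True usual-care control | Rule met | Rule met and observed reduction-arm control below 90% |
|---|---|---|
| 100% | 1% | 0% |
| 99% | 4% | 0% |
| 98% | 8% | about 0% |
| 95% | 33% | 7% |
| 92% | 69% | 36% |

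These figures ignore the practice random effect and baseline adjustment. Including them would change the probabilities somewhat, but not the floors in step 2.

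**The case against.** The sentence is a soft one. It says that meeting the margin will suggest the 9-in-10 result, in a paragraph that opens by assuming 100% usual-care control, and on that premise it is correct. Every participant enters controlled, so the sentence can also be read as being about control retained. The formal conclusion in the Statistical analysis section, and the aim in the Abstract, are comparative. Arm-level proportions with confidence intervals are ordinary SAP or results content, so their absence from the article is not a fault. All of this stands and limits the weight of the point. It does not rescue the sentence, because a planning value at the boundary cannot support a conclusion for patients once the data show something lower.

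Two stronger readings should be resisted.

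- A reader might infer that the test breaches its 2.5% level. With both arms truly at 80%, 85% or 88%, the rule is met in about 64%, 79% and 88% of trials. But the arms are equal in those cases, so declaring non-inferiority is correct and the figures are the power of the test. The 2.5% was never an error rate for a single-arm claim.
- A reader might infer that the protocol commits the trial to announcing 9 in 10 whenever the margin is met. It contains no such rule.

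**Conclusion.** The point holds as an error of interpretation. The article attaches an absolute, single-arm message to a comparative test, and the message follows only if usual-care control is 100%. The gap is small if usual care is at 98% to 99% and substantial at about 95% and below. Where the truth lies cannot be settled from the article, because any usual-care rate other than 100% is assumed. The non-inferiority test, its significance level, the sample size and the comparative conclusion are not called into question. The correction is worth making because the sentence is the sole stated reason for the margin and is directed at patients.

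**What to change.** Reword the interpretation in the Sample size calculation section to what the rule supports: for every 10 patients who would be controlled on usual care, at least 9 would be controlled under the reduction strategy.

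In the SAP or the report, give the reduction-arm proportion with its 95% CI beside the relative risk. Make an absolute 9-in-10 statement only if that interval supports it. Describe any such statement as applying to the reduction strategy: under intention to treat the arm includes participants whose medication was restarted, so it does not describe patients who stay on reduced medication.

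The cost is one sentence and one interval from data already collected, with no change to the primary test. The downside is that the simple message may be unavailable even when non-inferiority is met. If support is taken to mean a lower exact 95% limit of at least 90% (228 or more of 243 controlled), it is available in about 96% of trials at the planned 96% control and in about 84% at a true 95%.

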### Statistical analysis

A detailed statistical analysis plan will be agreed prior to the end of the trial. The primary and secondary analyses will be by intention to treat (ITT), unless stated otherwise. The primary analysis will be a non-inferiority analysis by means of the ‘two one-sided test’ procedure,^32^ whereby the 95% CI for the relative risk of participants with systolic blood pressure at 12 weeks below 150 mm Hg between the medication reduction group and the usual care group is calculated. This will be obtained by means of a generalised linear mixed effects model with GP surgery included as a random effect and baseline blood pressure as a fixed effect. If the lower limit of the CI is >0.9 (equal to a risk difference of 10%) then the research hypothesis that medication reduction will be non-inferior in terms of blood pressure control to usual care will be accepted. As a secondary analysis of the primary outcome, a per-protocol (PP) analysis will be performed, since ITT can be anticonservative for a non-inferiority hypothesis.^32^ Participants who received the medication reduction intervention in the PP analysis will be defined as a participant in the medication reduction arm who maintained their medication reduction throughout the 12-week follow-up period.

Secondary analyses will examine the proportion of participants in the medication reduction arm who maintained their medication reduction throughout the 12-week follow-up period. Secondary outcomes will be analysed by means of linear mixed effects models, adjusting for the baseline level of the outcome and baseline systolic blood pressure and including practice as a random effect: systolic blood pressure, EQ-5D-5L and the Frailty index/frail scale. The difference in the rate of side effects and AEs between the medication reduction and usual care arms will be analysed by means of a logistic mixed effects model adjusting for baseline systolic blood pressure and including practice as a random effect.

Exploratory subgroup analyses of blood pressure control, change in blood pressure and maintenance of medication reduction will be conducted by different levels of baseline frailty, functional independence, cognitive function, number of medications prescribed at baseline and number of comorbidities at baseline.

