## Methods

### Aims and outcomes

The aim of this study is to determine whether antihypertensive medications can be safely reduced without systolic blood pressure increasing beyond what is clinical acceptable at follow-up.

The primary outcome is the proportion of participants with clinically acceptable blood pressure levels at 12-week follow-up (defined as a systolic blood pressure <150 mm Hg). Secondary outcomes will examine:The proportion of participants in the intervention arm who maintain medication reduction through to follow-up (ie, are *not* restarted on therapy).The difference in quality of life (according to EQ-5D-5L) between groups at 12-week follow-up.The difference in frailty (according to the frailty index)^22^ between the two groups at 12-week follow-up.The difference in the change in mean clinic systolic blood pressure (from baseline) between the two groups at 12-week follow-up.The difference in reported side effects to medication between the two groups at 12-week follow-up (including coughs, dizziness, syncope, and ankle swelling).The difference in routinely reported serious adverse events (SAEs) between the two groups at 12-week follow-up (hospitalisation due to falls, myocardial infarction, stroke or all-cause mortality).

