**Figure 2 F2:**
[figure not shown]
Medication reduction algorithm. Screening Tool of Older Person’s Prescriptions (STOPP) criteria withdraw one of the following medications if any of the ensuing contraindications are identified: thiazide diuretic with a history of gout (may exacerbate gout), beta-blocker in combination with verapamil (risk of symptomatic heart block), non-cardioselective beta-blocker with chronic obstructive pulmonary disease (risk of bronchospasm), calcium channel blockers with chronic constipation (may exacerbate constipation), use of diltiazem or verapamil with New York Heart Association class III or IV heart failure (may worsen heart failure). GP, general practitioner; NICE, National Institute for Health and Care Excellence.

Once a medication has been removed, GPs or other appropriate, delegated healthcare professionals will closely monitor the participant’s response to medication reduction: they will be given advice about what and when to monitor (figure 3), but this schedule will be flexible. All participants will be expected to return for at least one routine safety follow-up visit, and further visits may be required if blood pressure is raised (≥150 mm Hg), or AEs occur. Where blood pressure is persistently raised, GPs will be expected to re-adjust medication (dose or type), rendering the likelihood of an SAE occurring as a result of the intervention very low.

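### The per-protocol set is selected on blood-pressure-triggered restarting, so it cannot serve as the conservative check on the ITT result that the protocol intends

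*Protocol article*

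**What the plan says.** All references are to the Protocol article.

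- **Purpose of PP (Statistical analysis).** ITT is primary. The article then says "As a secondary analysis of the primary outcome, a per-protocol (PP) analysis will be performed", and gives the reason: "since ITT can be anticonservative for a non-inferiority hypothesis".
- **Who counts as treated in PP (same section).** Only "a participant in the medication reduction arm who maintained their medication reduction throughout the 12-week follow-up period". No PP rule is given for the usual care arm.
- **Meaning of maintaining (Aims and outcomes).** The first secondary outcome is the share of the intervention arm "who maintain medication reduction through to follow-up", explained there as not being restarted on therapy.
- **What triggers re-treatment (Intervention group, text after Figure 2).** At the routine safety stage, "further visits may be required if blood pressure is raised (≥150 mm Hg), or AEs occur". Then: "Where blood pressure is persistently raised, GPs will be expected to re-adjust medication (dose or type").
- **Endpoint (Aims and outcomes).** "The primary outcome is the proportion of participants with clinically acceptable blood pressure levels at 12-week follow-up", with the cut-off at a systolic pressure below 150 mm Hg.
- **Follow-up (Follow-up visits).** Participants are asked to attend at week 12 whether or not medication has been re-introduced.

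**The concern.** A PP analysis helps in a non-inferiority trial when it removes departures that pull the arms together, so that a real difference can show. Here the main such influence is re-treatment of reduction-arm participants whose pressure rises. The PP rule does not undo that influence. It removes the people in whom the rise was seen and keeps those whose pressure stayed acceptable without the drug. The variable that decides membership is the endpoint variable, and the level that prompts further visits is the endpoint cut-off.

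Those removed are not deviators. Re-adjustment is part of the assigned strategy, and the Discussion contrasts this trial with an earlier one whose algorithm did not encourage reintroduction.

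PP is the only safeguard against an anticonservative ITT that this article states. If it cannot do that job, agreement between ITT and PP carries less weight than readers will give it.

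There is a second, smaller gap. Re-adjustment may be by dose or type, but maintenance is defined only as not being restarted. A participant whose remaining drug was escalated could count as having maintained the reduction and also as controlled. This affects the PP set and the maintenance outcome alike.

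**Working it through.** **1. The plan's own inputs.** The Sample size calculation section gives 100% versus 96% control, a 10% margin, 90% power, 2.5% one-sided, 10% loss and 10% dilution from cross-over. With the variance taken at the margin for the null:

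n = (1.960·√(0.90·0.10) + 1.2816·√(0.96·0.04))² / 0.06² = 195.6, so 196 per arm and 392 in total.

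392 / 0.9 / 0.9² = 538, against the stated 540. The figure reproduces. Evaluable participants per arm: 540 × 0.9 / 2 = 243.

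**2. How PP relates to ITT.** Let r be the share of the reduction arm restarted and c the week-12 control rate among them. Then

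PP rate = (ITT rate − r·c) / (1 − r).

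PP exceeds ITT exactly when c is below the ITT rate. Take r = 10%, treating all of the plan's cross-over as restarts in the reduction arm (an assumption), with ITT at 96%:

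- c = 100%: (0.96 − 0.10) / 0.90 = 95.6%
- c = 60%: (0.96 − 0.06) / 0.90 = 100%

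So on the plan's own figures PP could move either way, down a little or up by more.

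**3. Effect on the decision rule.** Now put the ITT rate at 90% against 100%, exactly at the margin. The probability that the lower 95% limit of the risk ratio exceeds 0.9 (binomial, 243 per arm, PP arm reduced by 10%, usual care fixed at 100%) is 0.04 for ITT. For PP:

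| c (assumed) | PP rate | Probability of meeting the rule |
|---|---|---|
| 100% | 88.9% | 0.01 |
| 90% | 90.0% | 0.04 |
| 80% | 91.1% | 0.12 |
| 70% | 92.2% | 0.27 |
| 50% | 94.4% | 0.76 |

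**4. Simulation of blood-pressure-triggered restarting.** Assumptions: underlying systolic mean 135 or 130, between-person SD 12, within-person SD 8, entry below 150, restart if the week-4 reading is 150 or more, full recovery after restart. The 7 mm Hg rise is the figure the Discussion cites from a trial of complete discontinuation. Risk ratios against usual care:

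| Mean | No restarts | ITT | PP |
|---|---|---|---|
| 135 | 0.864 | 0.921 | 0.948 |
| 130 | 0.908 | 0.942 | 0.959 |

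**5. How far this depends on the assumptions.**

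- In a grid of 24 scenarios (rise 5 to 15 mm Hg, half or full recovery, 0 to 25% of restarts unrelated to blood pressure), PP was above the no-restart value in all 24. It was above ITT in 15: all 12 with half recovery, 3 of 12 with full recovery.
- In a grid of 32 (mean 130 or 135, rise 7 or 12, half or full recovery, single or confirmed trigger, 0 or 10% unrelated restarts), PP was above the no-restart value in all 32 and above ITT in 27.
- With mean 130, SDs 8 and 10, a 7 mm Hg rise and 10% unrelated restarts, PP was 0.933 and ITT 0.938.
- At the extreme of a 15 mm Hg rise, full recovery and 25% unrelated restarts, PP was 0.775, ITT 0.878 and the no-restart value 0.604.

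The stable result is that PP lies above the no-restart value. Its order relative to ITT is not stable.

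**The case against.** **PP need not favour non-inferiority more than ITT.** A reader might infer that it always does. The documents do not support that. If re-treatment restores control by week 12, or if restarts follow adverse events and not raised pressure, PP can fall below ITT. This objection stands.

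**Re-treated participants are not the ones who fail the endpoint.** A reader might equate the two, but the endpoint is the week-12 reading. In the two tabulated simulations, 75% and 79% of those re-treated were controlled by then. This also stands.

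**The trial tests a strategy that includes re-adjustment.** The no-restart ratio of 0.86 is therefore not the truth for the primary hypothesis. With mean 135 the strategy's own ratio is 0.92, inside the margin, and a higher chance of PP meeting the rule is not a false-positive rate for the trial's question. This stands for the primary analysis. The no-restart value remains a fair yardstick for PP, because PP was added to guard against an ITT result that looks too favourable.

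**The inputs lean one way.** The 7 mm Hg comes from stopping all treatment, whereas here one drug is stopped. The simulated usual-care control rate at mean 135 is 91.5%, against the plan's 100%. The sizes are illustrative.

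**PP is secondary, and detail may sit in the analysis plan.** The article defers detail to a plan not shown, which may contain a usual-care rule. The share maintaining reduction and the change in mean pressure are also reported, so readers will see how many were dropped. This lowers the severity. But the reduction-arm criterion is fixed in this article, so it is not something merely left for later.

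**Conclusion.** The point holds and should be fixed, though it does not threaten the primary result. The PP criterion selects on a post-randomisation event that persistently raised pressure is expected to trigger, and removes participants treated as the protocol directs. It overstated control relative to no re-treatment in every scenario examined, so it cannot be relied on as the conservative check the article describes.

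An illustrative size is 0.86 without restarts, 0.92 in ITT and 0.95 in PP. This rests on assumed means and SDs, a rise borrowed from complete discontinuation, and full recovery after restart. The direction of PP against ITT should not be claimed as fixed.

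The formal conclusion rests on ITT and is unchanged. The cost of leaving the rule as it is would be false reassurance when ITT and PP agree. The loose definition of maintenance adds to this, because dose escalation is not clearly counted.

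**What to change.** 1. **Define PP by departure from the allocated strategy.** Reduction arm: one antihypertensive stopped as allocated. Control arm: no trial-type reduction. Both arms: eligible, with a week-12 blood pressure in the visit window. Do not exclude protocol-directed re-treatment.
2. **Address anticonservatism separately.** That PP set will lie close to ITT, so add one sensitivity analysis, applied alike in both arms, in which any antihypertensive restarted, added or increased before week 12 counts as not controlled.
3. **For the analysis, define maintained reduction** as no antihypertensive restarted, added or increased, and use that definition for the secondary outcome as well.

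Table 1, row 15 already collects drug, dose and start date at baseline and follow-up, so no new data and no change to care are needed. The cost is wording in the analysis plan, which the article says is still to be agreed, plus one extra analysis. The downside is that the sensitivity result will look less favourable than the planned PP and must be presented as a stress test, not as the estimate of the strategy's effect.
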